### Monitoring

The PI in each center will manage quality control by monitoring the administration of the trial in accordance with the protocol, applicable guidelines, and regulations. Monthly reports regarding the progress of the trial will be prepared by the Quality Control and Assurance Committee, including patient recruitment, randomization, protocol adherence, reports of AE/SAE and completeness of the data. All participating sites will have phase meetings and monthly monitoring visits to verify consent, eligibility criteria, anomalous data, and reported SAEs.

### Determination of the Sample Size

The sample size was set at 220 to provide at least 80% power (1-β) to detect an 23.3% absolute risk reduction in the primary efficacy outcome for patients in the glibenclamide group compared to those in the control group, using a test of two-sided significance with a 5% type I error (α). The rate of non-adherence to the treatment protocol and overall loss to follow-up is assumed to be 15%. In our pilot study, the volume of PHE in patients receiving glibenclamide was significantly smaller than control group at day 7 (21.74 ± 9.70 mL vs. 31.22 ± 10.16 mL, *p* = 0.038). At 90 days, 33.3% of patients in control group had unfavorable outcomes while the data was 10.0% for the patients assigned to glibenclamide group (Supplementary File 2).

### Statistical Considerations

Patients in our study will be analyzed according to the intention-to-treat principle. Analyses will be conducted by blinded biostatisticians. Baseline data will be analyzed using univariate analyses. Categorical variables will be presented as rates, whereas continuous variables will be expressed as median (interquartile range) or mean ± standard deviation. The primary and secondary outcomes will be compared between patients randomized to the glibenclamide group and the control group using the Chi-square test or Fisher's exact-test and the Student's *t*-test or Wilcoxon rank-sum-test. Logistic multivariate analyses will be used to adjust for potential confounding effects of different variables and estimate the adjusted odds ratios and associated 95% confidence intervals. Two-sided *p*-values < 0.05 in all tests will be considered significant. The statistical analysis will be performed with SPSS version 19.0 software (SPSS Inc., Chicago, IL, USA).

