## Methods and Analysis

### Study Objectives

The purpose of this hospital-based study is to assess whether small doses of oral glibenclamide would reduce edema and improve the prognosis in patients with ICH.

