### Study Procedures

Figure 1 presents the flow chart of the GATE-ICH trial. Based on the inclusion and exclusion criteria, the potential subjects offering informed consent will be randomized. At baseline, demographics, medical history (acute ischemic stroke, ICH, coronary events, diabetes mellitus, and hypertension), physical examination results, clinical scores (NIHSS, GCS, ICH score, Barthel index, mRS), vital signs, and head CT results will be recorded. Routine laboratory tests for patients with ICH will be conducted (routine blood tests, renal and liver function tests, serum lipid, fasting glucose, routine urine tests, electrocardiography, and head CT) on days 1, 3, and 7. Clinical scores (NIHSS, GCS, Barthel index, and mRS) on day 3 and day 7 or the day of hospital discharge will be collected. The Barthel index and mRS on day 90 will be assessed. During the entire period of hospitalization, concomitant treatments, adverse events (AEs), and serious AEs (SAEs) will be documented.

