#### Imaging Evaluations

A baseline CT evaluation of ICH volume will be performed by the investigators and study coordinators in each center using an image matrix of 512 × 512 with a slice thickness of 5 mm. The three CT assessments of the same subject should use the same type of CT. At an initial meeting, all investigators will be trained on the methodology of hematoma volume calculation using ABC/2 and provided with an electronic instruction manual. CT scans will be performed as standard procedures, and additional magnetic resonance imaging or other scans will be used when patients appear to have neurological deterioration. The final results of the three CT scans in every patient will be evaluated by independent investigators blinded to the clinical variables using the 3D Slicer software package (version 4.10.2; National Institutes of Health, Bethesda, MD, USA). ICH and PHE volumes will be measured using a semiautomatic volumetric algorithm as in a previous study (Figure 2) (22, 23).

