### Study Outcomes

#### Efficacy Outcomes

The primary efficacy endpoint is the percentage of unfavorable outcomes (mRS ≥3) at 90 days post-enrollment. The secondary efficacy endpoints include changes in the volume of ICH and PHE between the baseline and follow-up CT scans, and changes in the clinical scores between baseline and follow-up.

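### One p<0.05 rule covers every test, and the secondary outcomes, including edema, are unranked and unprotected; the primary is not affected

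*Protocol article*

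**What the plan says.** Study Objectives gives the trial a double aim: to see whether the drug "would reduce edema and improve the prognosis in patients with ICH". Efficacy Outcomes names one primary: "The primary efficacy endpoint is the percentage of unfavorable outcomes (mRS ≥3) at 90 days post-enrollment". The secondary endpoints are "changes in the volume of ICH and PHE between the baseline and follow-up CT scans" and "changes in the clinical scores between baseline and follow-up". No score, visit or volume is singled out, and no order is given.

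Statistical Considerations says that both the primary and the secondary outcomes will be compared between arms, and that two-sided p-values "< 0.05 in all tests will be considered significant". The article states no multiplicity rule, testing order or exploratory label.

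The visits come from two other sections. Imaging Evaluations refers to "The final results of the three CT scans in every patient". Study Procedures says: "Clinical scores (NIHSS, GCS, Barthel index, and mRS) on day 3 and day 7 or the day of hospital discharge will be collected". It then adds the Barthel index and mRS at day 90.

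**The concern.** The sentence on p-values is a decision rule. It attaches the word significant to any secondary comparison below 0.05, without regard to how many there are or what the primary shows. A list of related outcomes at several visits, each judged at 0.05, has a family-wise error above 5%.

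Edema is the second matter. It is half of the objective, and the Discussion repeats it in the trial's hypothesis. The limitations paragraph of the Discussion also says that, without a placebo, the main outcome is subjective and open to bias, while imaging outcomes are objective. Readers will therefore look closely at PHE. Under the present rule, day-7 PHE has the same standing as day-3 GCS: a true effect on it has no confirmatory status, and a chance finding elsewhere in the list can be called significant just as readily.

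**Working it through.** The article gives no family-wise error figure to reproduce, so the check counts the comparisons and computes the error rate under the stated rule.

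**Count, if every measure is tested at every scheduled follow-up**

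- Imaging: 2 volumes × 2 follow-up scans = 4 (Imaging Evaluations, reading the three scans as baseline, day 3 and day 7).
- Early scores: NIHSS, GCS, Barthel and mRS × 2 times = 8 (Study Procedures).
- Day-90 scores: Barthel and mRS = 2 (Study Procedures).
- Total: 4 + 8 + 2 = 14, or 13 if the day-90 mRS change is set aside because it overlaps the primary.

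The adjusted logistic analyses and the safety outcomes are not counted. The alternative reading is one comparison for each of six measures (PHE, ICH volume, NIHSS, GCS, Barthel, mRS).

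**Independent tests, no effect on any outcome**

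P(at least one p<0.05) = 1 − 0.95^m.

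- m = 14: 1 − 0.95^14 = 51.2%; expected false positives 14 × 0.05 = 0.7
- m = 13: 48.7%
- m = 6: 1 − 0.95^6 = 26.5%
- m = 4 (all imaging tests): 18.5%
- m = 2 (PHE at two times): 1 − 0.95^2 = 9.75%

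**Correlated tests**

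The article gives no correlations, so these are assumed. Fourteen equally correlated standard normal test statistics were simulated (400,000 draws), with |z| > 1.96 counted as significant. The last column counts only results favouring glibenclamide; its independent-case value also follows from 1 − 0.975^14 = 29.8%.

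| Correlation | At least one, either direction | At least one favouring glibenclamide |
|---|---|---|
| 0 | 51% | 30% |
| 0.3 | 44% | 22% |
| 0.5 | 35% | 17% |
| 0.7 | 25% | 12% |
| 0.9 | 14% | 7% |

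A mixed pattern (0.6 among imaging tests, 0.7 among scores, 0.3 between the two groups) gives 31%.

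**Effect of the proposed sequence**

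The primary is tested at 0.05, and day-7 PHE change at 0.05 only if the primary is significant. Family-wise error for these two claims is at most 5%, and the primary keeps its full alpha.

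For the PHE test itself, take the pilot figures in Determination of the Sample Size: difference 31.22 − 21.74 = 9.48 mL, pooled SD √[(9.70² + 10.16²)/2] = 9.93 mL. Use 110 per arm, or 93 after the assumed 15% (220 × 0.85 / 2 = 93.5). At half the pilot difference, 4.74 mL, power at 0.05 is 90% (93 per arm) to 94% (110 per arm). Bonferroni over 14 tests (0.05/14 = 0.0036) would give 63% to 73%. These figures assume that the pilot day-7 SD applies to change from baseline, for which the article gives no SD. They describe the PHE test once it is reached.

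**The case against.** The strongest reply is that the confirmatory claim is already safe. There is one primary endpoint at one time, the sample size uses that endpoint and a two-sided 5% alpha, and everything else is labelled secondary. That stands: testing secondaries does not raise the primary's type I error.

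A second reply is that a key secondary, a testing order and an exploratory label are details an article may leave to a full protocol or SAP not shown here. Their absence alone would be no finding. But the article does set a threshold for all tests, and a hierarchy elsewhere would have to override that sentence.

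Third, the count of 14 is a reading. Study Procedures describes what is collected, and Efficacy Outcomes does not say that each score is tested separately at each visit. This also stands, and is why the six-measure figure is given beside it.

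Fourth, a reader might infer that a false significant secondary result, or a false edema result in particular, is likely. The documents do not support that. Only independence with 14 tests passes even odds, and independence is not credible for the same patients measured repeatedly on related scales and scans. Results that could be mistaken for benefit are 30% or less, and false PHE results about 10% or less. Nor does the article say that a secondary p-value would be claimed as efficacy if the primary failed; the rule allows such wording but does not commit to it.

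Finally, the fixed sequence does not give PHE confirmatory standing when the primary is null. This is a true limit of the remedy. Placing function above edema is a legitimate choice.

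**Conclusion.** The point holds as a badly fixed rule for secondary claims, worth correcting, with no bearing on the validity of the primary test. If no effect exists and about 14 tests are done, the chance of at least one false significant secondary is at most about 51%, and roughly 25–44% at correlations of 0.7–0.3. With six tests it is at most 26%. For results favouring glibenclamide, 14 tests give 30% if independent and 17% at correlation 0.5. The sizes rest on the reading of the visit schedule, on assumed correlations, and on no true effect on any secondary outcome. Even the lower figures are several times 5%, apart from the PHE tests taken alone (at most about 10%) and very high correlations.

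**What to change.** In Statistical Considerations, replace the all-tests rule with a stated sequence: the primary at two-sided 0.05; then, only if it is significant, change in PHE volume from baseline to day 7 at two-sided 0.05. In Efficacy Outcomes, name that change as the one key secondary. Report all other secondary outcomes, including PHE at day 3, with estimates and 95% confidence intervals, labelled exploratory and without significance claims. Record the change before anyone sees outcome data by arm.

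The cost is wording only; sample size and visits stay as they are, and the primary loses no power. The downside is that no formal claim can be made on the other secondaries, and PHE has confirmatory standing only when the primary is significant. If the primary is null, PHE is reported as an estimate with its confidence interval.

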### Patient and Public Involvement

Patients were not involved in the design of the study. The burden of intervention and the participation time in the research will not be assessed by the patients themselves. During the treatment stage, analysis of adverse reactions (such as symptoms of low blood sugar) will require timely feedback from the patients, assessment of the investigators, and confirmation by assessment instruments. At the termination of the trial, a scientific article will be authored to present the main results, and a brief summary of the results in plain language will be provided to all participants.

### Protocol Amendments

Any amendments to the protocol will be requested with the agreement of the GATE-ICH Study Group, Sponsor, and Funding Body. Following approval by the ethics committee, the modifications to the protocol will be communicated to the trial investigators and the trial registry (and if required, to the trial participants).

## Discussion

The GATE-ICH trial is a multicenter, randomized, controlled, assessor-blinded clinical trial in China. We will assess the hypothesis that small doses of oral glibenclamide is an effective method to reduce the PHE after ICH and to improve the 90-day prognosis of patients. The trial will provide new evidence regarding the management of PHE in patients with ICH.

In patients with supratentorial ICH, the hematoma volume was one of the important factors predicting outcomes (1). Patients with massive ICH (volume >30 mL) were associated with an increased risk of poor outcomes, and might respond better to surgical treatment rather than conservative treatment (24, 25). In addition, the clinical outcomes were not influenced by the PHE in patients with hematoma volume >30 mL no matter the location (10, 26). Results of previous studies found that the effect of PHE on 90-day unfavorable outcome was more relevant in patients with hematoma volume <30 mL than those with massive ICH (26–29). In patients with hematoma volume <30 mL, there was a significant association between PHE and poor outcome in basal ganglia ICH (10, 26). However, the relationship of PHE and poor outcome was controversial in lobar ICH (10, 26). Thus, basal ganglia hematomas with volumes <30 mL could be regard as an optimal target for interventions designed to ameliorate PHE after ICH (10).

Although the conservative treatment was usually suggested in patients with hematoma volume <30 mL, there are few effective therapies available for treatment of PHE after ICH (25). Traditional dehydration therapy is the most common option in clinical practice; however, its' effect is modest (7, 30). Identifying anti-edema drugs may be a promising intervention for ICH. As a candidate anti-edema drug, glibenclamide has been proven effective for the treatment of brain swelling after large hemispheric infarction in humans (12). In the GAMES-Pilot study, vasogenic edema appears to be reduced in patients with acute ischemic stroke treated with glibenclamide (16). It has been verified that glibenclamide could improve the injury of ICH through its' anti-inflammatory effects and scavenging of free radicals in pre-clinical studies (14, 15). Our study aims to test the efficacy of glibenclamide for treating edema and improving 90-day outcomes after ICH in a treated group compared to a control group in human subjects.

The GATE-ICH study is a multicenter randomized, controlled, assessor-blinded trial. Some limitations of this trial should also be noted. First, as a definite limitation in this trial, the placebo control was originally designed at the beginning of the design phase. However, unexpected failure of the placebo production line forced us to adjust initial study protocol from the placebo control to the blank control. After rigorous evaluation, the main outcome was a subjective outcome indicator and might be biased by the placebo effect, while both of imaging outcomes and safety outcomes were objective outcomes with limited placebo effect. In order to avoid the influence of placebo effect as much as possible, the outcomes evaluation and statistical analysis would be blindly processed by independent researchers throughout the study. Second, some background treatments were not standardized. For example, the selection of osmotherapy medicines depended on local availability in patients with intracranial hypertension. Thus, background treatments should be standardized as much as possible in future studies. Last but not least, the population was limited to the Chinese patients, which might restrain generalizability of the results to other populations. Thus, multicenter research in more countries will be needed.

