### Trial Interventions

#### Intervention Arms

The time course of plasma glibenclamide levels indicates that an oral formulation of 3.5 mg/day at 4 h after administration is equal to an intravenous formulation of a 0.13-mg bolus followed by a dose of 3 mg/day, which has been proved efficacious and safe for treating edema in patients with ischemic stroke (13, 19). The half-life of glibenclamide is 4.0–13.4 h in elderly patients and 4.0–13.9 h in younger patients (20). In order to achieve a stable drug concentration that coincides with three mealtimes, we chose a dose of 1.25 mg, 3 times per day (3.75 mg/day). In our pilot study, 10 patients in the glibenclamide group and 12 patients in the control group were enrolled. The plasma concentration of glibenclamide elevated to 47.6 ng/mL at 2 h after the first dose, and gradually achieved by steady state plasma concentration of glibenclamide at 72 h (26.7 ng/mL). Patients assigned to the glibenclamide group will receive tablets containing 1.25 mg of glibenclamide [Yun Peng Pharmaceutical Co., Shanxi, China; each capsule (2.5 mg)] three times daily (no more than 30 min before a meal) for 7 consecutive days after enrollment in addition to the usual care and medications for ICH. Patients in the control group will receive only the usual care and medications for ICH. Glibenclamide tablets should not be administered after head CT on day 7. Treatment with other SFU agents is not permitted during the 90-day follow-up period in either group.

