#### Safety Outcomes

The safety endpoints include the BG-related safety and cardiac-related safety of glibenclamide tablets as follows: (1) hypoglycemia (BG <3.1 mmol/L), (2) symptomatic hypoglycemia (hypoglycemia with confirmed hypoglycemic symptoms), (3) incidence of cardiac AE/SAEs or a QT interval of >500 ms, and (4) incidence of all-cause mortality.

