### Blinding

The outcome assessors and data analysts will be blinded to the interventions. There will be one investigator assessing the functional outcomes in every center who will be blinded to the intervention received by the participants. All of the imaging evaluations will be conducted by independent investigators blinded to the clinical variables, interventions, and functional outcomes. The analyses will be conducted by blinded biostatisticians.

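### In defending the blank control, the Discussion calls all safety outcomes objective, but the symptom part of symptomatic hypoglycemia and the reported cardiac AE/SAEs are not, and are open to differential ascertainment

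*Protocol article*

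**What the plan says.** The Discussion lists the lack of a placebo as a definite limitation. It gives the cause as a failed placebo production line, which "forced us to adjust initial study protocol from the placebo control to the blank control". It then concedes that the main outcome is subjective, and states that "both of imaging outcomes and safety outcomes were objective outcomes with limited placebo effect", with no exception for any safety endpoint. As mitigation it adds that outcome evaluation and analysis will be done blind by independent researchers.

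Safety Outcomes lists four endpoints: hypoglycemia (BG below 3.1 mmol/L); "symptomatic hypoglycemia (hypoglycemia with confirmed hypoglycemic symptoms"); "incidence of cardiac AE/SAEs or a QT interval of >500 ms"; and all-cause mortality.

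Patient and Public Involvement describes how adverse reactions are established: "analysis of adverse reactions (such as symptoms of low blood sugar) will require timely feedback from the patients, assessment of the investigators". The same sentence goes on to require confirmation by instruments.

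On masking, Intervention Arms states that "Patients in the control group will receive only the usual care and medications for ICH". The Blinding section opens with a general sentence that outcome assessors and analysts are blinded. It then gives specific arrangements for two kinds of assessment only. For function, "There will be one investigator assessing the functional outcomes in every center who will be blinded"; for imaging, there are independent blinded readers.

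**The concern.** A safety outcome resists bias in an open trial when its detection does not depend on anyone who knows the arm. A glucose value from a scheduled check, a QT interval and a death meet that standard or come close to it. A symptom that the patient must mention and the investigator must judge does not, nor does a cardiac event that someone must notice and record.

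Patients who know that they take a sulfonylurea, and staff who watch for its known effects, may report and record such events more readily than in an arm that takes nothing. BG-related and cardiac safety are the stated safety focus of the trial. A difference between arms in these components could therefore be partly a difference in looking and asking. A reader who accepts that all safety outcomes are objective would not allow for that.

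**Working it through.** No figure in the article tests this point, so the check sets the relevant sections side by side.

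1. *Who knows the arm.* Controls receive no matching tablet (Intervention Arms). Patient Safety has staff act on the study drug according to glucose values, and Medical Care in the Hospital singles out glibenclamide patients with poor intake for glucose. Staff cannot follow these sections without knowing the arm, and nothing masks the patient. That the people who record AEs also know it is an inference from the open design. Study Procedures says that AEs and SAEs are documented during hospitalization, but not by whom.

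2. *What each safety endpoint rests on.*
 - Hypoglycemia: a measured glucose value.
 - Symptomatic hypoglycemia: that same value plus confirmed symptoms.
 - Cardiac endpoint: a measured QT interval, or a reported cardiac AE/SAE.
 - All-cause mortality: a hard event.

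 Two of the four endpoints therefore contain a component that depends on reporting.

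3. *How far the bias can reach in symptomatic hypoglycemia.* By definition, symptomatic cases in an arm = (patients with BG below 3.1 mmol/L) × (share of them with confirmed symptoms). Readier symptom reporting can act only on the second factor, so the symptomatic count can never exceed the hypoglycemia count in that arm. The glucose factor is scheduled identically in both arms: 3 checks a day × 7 days = 21 checks per patient (BG Monitoring). That section adds checks at least every 2 hours during hyperglycemia. If hyperglycemia differs between arms, so does the number of chances to find a low value, and the glucose comparison is cleanest on the scheduled checks alone.

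4. *How far it can reach in the cardiac endpoint.* Electrocardiography is scheduled on days 1, 3 and 7 (Study Procedures), which supports the QT limb. The AE/SAE limb has no such gate. Because the endpoint joins the two with an *or*, the combined rate inherits the weakness of the reported limb.

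5. *Whether the stated blinding closes the gap.* Even if the general blinding sentence and the Discussion's blinded evaluation are read as covering safety events, both operate after an event has been elicited and written down. The monthly visits under Monitoring verify SAEs that were reported. None of these can recover a control-arm symptom that nobody asked about.

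**The case against.** Several points on the other side are sound, and they shape the conclusion.

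- A reader might infer that the placebo was dropped because the safety outcomes were thought objective. The article does not support this. The stated cause is the production failure, the passage is presented as a limitation, and objectivity is argued afterwards to defend living with the open control.
- The Discussion sentence speaks of placebo effect and does not claim equal ascertainment. That is so, but the premise it uses, that the outcomes are objective, is still wrong for two components, and reporting bias is not mentioned.
- Symptomatic hypoglycemia is anchored by the glucose threshold and by instrument confirmation. This narrows the bias to the symptom part. It does not remove it, because confirmation follows feedback and assessment.
- A reader might infer that the plan formally tests these outcomes as if ascertainment were equal. Statistical Considerations names tests for the primary and secondary outcomes only; no comparative safety test or safety claim is set out.
- A reader might fear false reassurance about the drug. The likely direction is the opposite, towards too much apparent harm on glibenclamide. Efficacy results are not touched.
- It is tempting to attach a risk ratio to the bias by assuming how much less the control arm reports. Any such figure would come from the assumption. It would also have to suppose equal true rates of hypoglycemia with and without a glucose-lowering drug, which the article's own safety provisions do not suggest.
- Detail on who adjudicates events may stand in the full protocol, which is not shown. Its absence from the article is therefore not held against the plan; the unqualified statement is.

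**Conclusion.** The point holds in a limited form. The statement that all safety outcomes are objective conflicts with Safety Outcomes and with Patient and Public Involvement. It fails for the symptom part of symptomatic hypoglycemia and for the reported cardiac AE/SAEs, that is, for one component in each of two of the four listed endpoints. It stands for the QT limb and mortality, and for the glucose value when compared on scheduled checks.

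These two components are open to differential ascertainment, most likely inflating apparent harm on glibenclamide. That direction is a judgement that rests on patients and treating staff knowing the arm, and on the recorders of AEs being among those staff or relying on them. The size cannot be derived from the article. The documents do not support a wider conclusion that the safety assessment as a whole is unreliable.

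**What to change.** (a) In the Discussion, limit the word objective to the BG value, QT above 500 ms and all-cause mortality, and name reporting bias as a consequence of the blank control. Base the between-arm safety conclusion on those three, with BG compared on the scheduled daily checks. Report QT separately from cardiac AE/SAEs. Present symptomatic hypoglycemia and cardiac AE/SAEs as open-label results subject to reporting bias.

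(b) Add the same short symptom item in both arms at the scheduled BG checks, at least whenever BG is below 3.1 mmol/L, so that symptoms are asked for in the same way and do not depend on spontaneous feedback.

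The blinded functional assessor at each center should not be used to classify these events. Hypoglycemia records can reveal the arm even with the label masked, that person rates the subjective primary outcome, and Post-discharge Follow-Up requires assessors who took no part in treatment or other trial work.

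The cost of (a) is wording and a weaker safety claim for two components. The cost of (b) is one item on an existing form, introduced through the amendment route. Recruitment is under way, so the item would cover only patients treated after the change. Some patients cannot answer it, since a GCS as low as 6 is eligible. It equalizes the prompting, but the patients who answer still know their arm, so the open-label caveat in (a) remains necessary.
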